#### Trial eligibility criteria

Trials will be eligible for inclusion in TRECA if they are recruiting within the UK and involve testing an intervention with children and adolescents who have a long-term health condition. Within each embedded trial, participants will be children and adolescents being asked to participate in the host healthcare trial and/or their parents. This is critical, as it means that the host trial and the embedded trial have different sample sizes. For the host trial the sample comprises those children and adolescents/parents agreeing to participate; for the embedded trial of the MMI resources the sample comprises those asked to participate. In some trials, the number asked to participate is much larger, often more than double the host trial sample size.

Eligible trials should ideally have a sufficient sample size to detect a difference between groups in the embedded trial; trials will be using only printed or video participant information materials as standard (i.e. not already including an MMI resource), and will be recruiting at least some children and adolescents who have the potential to contribute to a decision about consent or assent to participation in the trial. Trials will not be included if they are only recruiting children too young to understand an MMI resource (e.g. children aged under 5 years), or only children with intellectual impairment such that understanding or use of the MMI resource is not possible.

We will aim to ensure that eligible trials vary with respect to the long-term health condition (using PRISM study criteria), the age of children and adolescents being recruited into the trial, host trials unit, the type of intervention (e.g. pharmaceutical, physical therapy, psychological), and the way that the MMI resource will be presented to patients (e.g. parent and child viewing together versus adolescent viewing separately to parent).

#### Method of embedding MMI into trials

Each of the embedded trials will use a three-arm design, in which individuals will receive the standard written trial PIS alone, the standard PIS in addition to the MMI resource, or the MMI resource alone (Fig. 2). We will consider making the written PIS available via the MMI resource, for example, by a link within the MMI resource to read or print the PIS document. This would have the advantage of being more efficient, allowing people to access both the MMI resource and the PIS via the computer. However, we will consider important practical concerns such as text readability on screens and participant preferences, and so will seek the opinions of participants in the focus groups during the development study phase. We will also measure the number of page views and the frequency which individual elements of the MMI resource are viewed.

Patients allocated to the control arm of the embedded trial will be given the printed PIS only (as is usual). Those allocated to one of the intervention arms will receive either the MMI resource alone or the printed PIS and the MMI resource(s). We will not determine the order in which participants access the PIS and MMI resource (for those participants who receive both) and will leave this for the host trial to determine, to suit the practical demands of patient recruitment. However, we will ask the host trial to record the order in which participants are given and access the PIS/MMI resource, and report this observation in the report of each embedded trial. The MMI resources will be presented in the clinic on a computer or dedicated tablet computer. Participants will also be able to access the MMI resources at home (via smartphone or a tablet or PC) via a link that is emailed to them. In some circumstances, home viewing will take place before the patient’s decision on clinical trial participation has been taken. Some patients will also want to be given access to the MMI resource after they have decided to take part in the host healthcare trial, just as they would if they had been given standard printed information only.

#### Outcome measures

The primary outcome will be the rates of recruitment to each host trial. We will calculate the proportion of patients who agree to participate from the total number approached, for each arm of the embedded trial. This study is investigating whether MMI resources improve the quality of decision-making, related to individuals being more informed about the trial. Improved decision-making may have no impact on trial recruitment rates, although it is also possible that it could either increase or decrease rates as a result of individuals being more informed. It is therefore important that we also measure secondary outcomes of retention in the trials, and quality of decision-making. We will measure retention by obtaining data on the number and timing of drop outs from each host trial. The quality of decision-making by potential host trial participants will be measured through the completion by children, adolescents and parents (as relevant) of a decisional scale, adapted from one used within the REFORM trial [57] and drawing conceptually on the SURE [58] and DelibeRATE scales [59, 60]. We will report study results in line with published guidelines [61].

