### Phase two: evaluation of MMI resources

#### Embedded trials of MMI resources within host clinical trials – design

The effectiveness of the two MMI resources will be evaluated in a series of trials embedded within six host trials in the UK (see Fig. 4 for Phase two design) that are recruiting children and adolescents with long-term health conditions, using methods we have developed previously [47]. That is, participants in each host trial will be allocated randomly to one of two or more different intervention groups. The embedded trial (aka nested trial or ‘trial within a trial’) will be run with potential participants in each host trial – these people will be allocated randomly to receive either the MMI resource plus the printed information, the MMI resource alone, or the printed information alone, to evaluate their relative effects on recruitment rates (and the secondary outcomes).

The objective is to test the effects of the MMI resources on cognition and behaviour. The primary outcome will be whether rates of recruitment to the host trials are increased. We will also test (1) whether individuals who see the MMI resource(s) make a more informed decision about trial participation (or not); (2) whether rates of retention in the host clinical trials are increased; and (3) whether individuals are more satisfied with the process of consent or assent.

Recruitment of host trials will occur through the National Institute for Health Research Clinical Research Network, funding bodies and through investigator networks. In previous qualitative work [56], we have identified that, while trialists welcome the idea of embedding trials of recruitment interventions in their studies, these need to be compatible with the host trial design and not impose an extra workload. In the embedded trials, allocation to groups will be achieved by random number generator. Particularly, in trials in which we use individual randomisation to the MMI resources, it will be practicably very difficult to achieve concealment of randomisation. Trials will use individual or cluster randomisation. Masking of the allocation at outcome measurement will not be possible since patients cannot be masked to the information format they will receive but, as they will be unaware of the embedded information trial, a lack of masking will not bias their responses or decisions.

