#### Sampling considerations

The projected effect of the MMI resources will vary in size according to the setting of the host trial, the background recruitment rate, and the intervention being tested in the host trial. This makes it difficult to establish a sample size calculation for each of the six embedded trials. The effectiveness of the MMI resources is being assessed against three outcome measures, namely host trial recruitment rate, quality of decision-making on participation (or not) and host trial retention rate. Results from each embedded trial will be combined in a prospective meta-analysis for decision scores and recruitment rate data from all six host trials participating in the TRECA study.

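### The primary rate counts agreements among patients approached, but where recruiting staff know or can foresee the arm, allocation can affect who is approached, so arms can differ in either direction without any MMI effect

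*Protocol article*

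**What the plan says.** The Outcome measures section of the protocol article defines the primary outcome, host-trial recruitment, as follows: "We will calculate the proportion of patients who agree to participate from the total number approached, for each arm of the embedded trial". The section on trial eligibility criteria uses the same population: "for the embedded trial of the MMI resources the sample comprises those asked to participate". No other denominator is given for any type of host trial.

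The section on the design of the embedded trials allows two units of allocation: "Trials will use individual or cluster randomisation". It does not say how many of the six host trials will be of each kind. With particular reference to individually randomised trials, it says that "it will be practicably very difficult to achieve concealment of randomisation". On masking, it argues that "as they will be unaware of the embedded information trial, a lack of masking will not bias their responses or decisions".

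On delivery, the section on embedding MMI into trials says: "The MMI resources will be presented in the clinic on a computer or dedicated tablet computer". It also provides for viewing at home through an emailed link. The section on sampling considerations plans to pool recruitment rates from all six host trials in a prospective meta-analysis.

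**The concern.** A proportion with the number approached as its denominator is protected by randomisation only if allocation cannot affect who is approached. Two features of the design put that in doubt.

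- **Cluster allocation.** The site is allocated first and its patients are approached afterwards. A site that delivers a given format in clinic will know which format it has. Being approached is then an event after allocation.
- **Individual allocation without concealment.** If staff can see or foresee a patient's arm before deciding whether to approach, the same route is open. The article itself says that concealment will be hard to achieve here.

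The article's reassurance rests on patients not knowing about the embedded trial. That bears on how patients respond once asked. It does not bear on which patients staff ask.

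At stake is the primary comparison. An arm that approaches fewer unlikely consenters shows a higher agreed/approached rate while the host trial gains nobody. Through the planned meta-analysis, a bias in one host trial carries into the pooled estimate.

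**Working it through.** **What can be reproduced.** Nothing numerical. The article gives no recruitment rate, effect size, alpha, power or intracluster correlation, and on sample size it says: "This makes it difficult to establish a sample size calculation for each of the six embedded trials". The figures below are illustrations on assumed inputs.

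**Assumed inputs.** Eligible patients fall into two equal halves, likely and unlikely to agree, with agreement probabilities a and b that are the same in every arm. There is therefore no MMI effect. One arm approaches everyone. The other approaches all likely patients and a share s of the unlikely ones. Although "Each of the embedded trials will use a three-arm design", a single pair of arms is enough to show the mechanism.

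**Formulas.**

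- Rate per approached = (0.5a + 0.5sb) / (0.5 + 0.5s)
- Rate per eligible = 0.5a + 0.5sb

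With s = 1, both equal 50% for a = 0.7, b = 0.3 and for a = 0.6, b = 0.4.

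**Example.** For a = 0.7, b = 0.3, s = 0.8, the numerator is 0.35 + 0.12 = 0.47 and the denominator is 0.90. The rate per approached is 0.47/0.90 = 52.2%, and the rate per eligible is 47.0%.

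| a, b | s | Approached/eligible | Agreed/approached | Difference from 50% (points) | Agreed/eligible |
|---|---|---|---|---|---|
| 0.7, 0.3 | 0.9 | 95% | 51.1% | +1.1 | 48.5% |
| 0.7, 0.3 | 0.8 | 90% | 52.2% | +2.2 | 47.0% |
| 0.7, 0.3 | 0.7 | 85% | 53.5% | +3.5 | 45.5% |
| 0.7, 0.3 | 0.5 | 75% | 56.7% | +6.7 | 42.5% |
| 0.6, 0.4 | 0.9 | 95% | 50.5% | +0.5 | 48.0% |
| 0.6, 0.4 | 0.8 | 90% | 51.1% | +1.1 | 46.0% |
| 0.6, 0.4 | 0.7 | 85% | 51.8% | +1.8 | 44.0% |
| 0.6, 0.4 | 0.5 | 75% | 53.3% | +3.3 | 40.0% |

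**The same in counts.** Take 100 eligible patients per arm, of whom 50 would agree under either format. If one arm skips 10 patients who would agree at 30%, it recruits 50 − 3 = 47 of 90, or 52.2%, against 50 of 100 in the other arm. Its rate is higher although three fewer patients joined. In the extreme case, where all 10 skipped patients would have refused, the rate is 50/90 = 55.6%.

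**Reading.** The sign follows whichever arm is selective. If the printed-sheet arm skips unlikely patients, the same differences count against the MMI. The approached/eligible column shows the selection directly. Agreed/eligible also moves away from 50%, so it reveals selective approach but does not isolate the effect on patients' decisions.

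**The case against.** The case on the other side has four parts.

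1. **Nothing is contradictory.** The embedded sample and the primary denominator match, and agreed/approached is a coherent measure of how the format affects people who receive it. This is true, and it is why agreed/approached need not be dropped in cluster trials. It does not answer the point that allocation may shape who is approached.

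2. **Staff discretion is not documented.** No section says that staff choose whom to approach. That a cluster site knows its format is a near-unavoidable inference from delivery in clinic. That its staff use discretion is only a possibility. This stands, and it limits the claim to what can happen.

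3. **The direction is unknown.** A reader might infer that showing material on a clinic device takes more effort than handing over a sheet, so that MMI sites would be choosier and their rates inflated. The document does not support this. It also offers home access by emailed link, one MMI arm has no printed sheet, and the design section recognises that embedding must not add to host-trial workload. A reader might also take individual randomisation to be the safe case, yet the article's explicit admission on concealment concerns exactly that case.

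4. **Safeguards may be in the full protocol.** Screening procedures and flow reporting are often left out of an article, and their absence here is not the complaint. The complaint is that the article itself fixes one denominator for both designs and sets bias aside with an argument limited to patients.

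A stronger remedy is also tempting: making agreed/eligible the primary rate in cluster trials. The case for it is weak, because unmasked staff may complete the eligibility log after allocation, so the log may itself be selected.

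**Conclusion.** The concern holds as a risk to the primary outcome that the stated rule leaves open, not as a demonstrated bias. One denominator, patients approached, applies to every host trial. Under cluster allocation, or under individual allocation that staff can foresee, being approached can depend on the arm, and the protocol's masking argument does not reach that step.

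Neither size nor direction can be derived from the document. The illustrative 0.5 to 6.7 points rest on an assumed 50% agreement rate, an assumed split into likely and unlikely patients, and selection in one arm only. The reach is also unknown, because the number of cluster-randomised host trials is not stated. The point should be settled before Phase two recruitment, which the article reports as not yet begun: patients who were eligible but not approached, if never logged, cannot be recovered at analysis.

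**What to change.** **Individually randomised host trials.** Define the primary denominator as all randomised patients, whether or not they were then approached. This closes the gap between allocation and approach. It does not prevent selection before randomisation if the next allocation can be foreseen, so patients should be entered before their allocation is revealed wherever that can be arranged.

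**Cluster-randomised host trials.** Keep agreed/approached as the primary rate, and add three requirements:

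- log eligible patients, where possible before the site's allocation is known or by staff unaware of it;
- report approached/eligible by arm;
- pre-specify agreed/eligible as a sensitivity analysis, and repeat the meta-analysis with it.

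The masking paragraph should also say that its argument concerns patients, and address recruiting staff separately.

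**Cost.** Small if host trials already keep screening logs, which is assumed here. The value of the sensitivity analysis depends on the quality of those logs. Agreed/eligible rates will be somewhat lower than agreed/approached, and they mix any effect on approach with the effect on patients' decisions. They should be read beside the primary rate and not in place of it.

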#### Sampling considerations

The projected effect of the MMI resources will vary in size according to the setting of the host trial, the background recruitment rate, and the intervention being tested in the host trial. This makes it difficult to establish a sample size calculation for each of the six embedded trials. The effectiveness of the MMI resources is being assessed against three outcome measures, namely host trial recruitment rate, quality of decision-making on participation (or not) and host trial retention rate. Results from each embedded trial will be combined in a prospective meta-analysis for decision scores and recruitment rate data from all six host trials participating in the TRECA study.

### PPI

The Investigators and research team have a strong commitment to PPI in the TRECA Study. TRECA has a Patient and Parent Advisory Group which will play a key role in reviewing and providing input into documentation used in the various stages of the study, including topic guides and prototype MMI resources. The Patient and Parent Advisory Group will also participate in the piloting of user testing questionnaires to ensure that the question wording and length are appropriate. Two members of the Patient and Parent Advisory Group are also members of the TRECA Study Advisory Group and one or two PPI members will be involved in co-facilitation of the second set of focus groups.

## Discussion

Whilst trials have been undertaken for many decades in medicine, limited data is available about the decision-making processes for trial participants and which information is important for them when considering whether to participate [2, 21, 52]. Studies that have examined the information needed for potential participants to make such decisions often do not include the level of detail that participants wanted to receive [52]. The numbers of studies looking at this issue in relation to children, adolescents and their parents, is limited [19, 20, 22, 53].

The TRECA study will identify the information that children and adolescents consider to be most important when deciding whether or not to participate in clinical trials. Informed by the principles of participatory design, we will produce MMI resources that aim to meet children, adolescents and their parents’ needs and preferences for information content and presentation. In particular, this should lead to improved patient information resources that offer relevant information in a way that is accessible to all potential participants, whilst also increasing their understanding of clinical trials in general. Ultimately, it is anticipated that improving participant information resources will increase participation in clinical trials. Specifically, this study will lead to the development of two MMI resources that are suitable for children and adolescents invited to future clinical trials. The findings may also be of use to researchers in different settings, such as education or mental health, in order to better inform and recruit participants to studies. It may also identify principles that are transferable to other medical settings where providing accessible information is crucial, for example, regarding patient decisions about hospital procedures or treatment options.

Results from the TRECA study will be published in peer-reviewed journals and disseminated widely through conferences and events. Where possible, we will also use social media to publicise the findings. In particular, we will aim to engage with health charities, self-help groups and lobbyists, with a view to informing children and adolescents with a variety of long-term health conditions who may be involved in research.

### Trial status

Phase one of the study has commenced. Recruitment for Phase two has not yet commenced.

## Abbreviations

MMI: multimedia information
PIS: participant information sheet
PPI: patient and public involvement
TRECA: TRials Engagement in Children and Adolescents
